### Criteria for discontinuing or modifying allocated intervention {11b}

If the therapeutic is found to cause harm to participants (e.g., increase in suicidal ideation or substance use), the trial will be stopped.

### Strategies to improve adherence to interventions {11c}

All therapy sessions will be digitally recorded, and adherence to treatment procedures will be evaluated using the Cognitive Therapy Rating Scale (CTRS) (Young JE, Beck AT: Cognitive therapy scale, Unpublished manuscript. Yurica CL: Inventory of cognitive distortions: Development and validation of a psychometric test for the measurement of cognitive distortions, Doctoral dissertation) and SBOA rating scale by PI [name]. A random sample of 20% of sessions will be coded to ensure that the procedures are delivered as intended.

### Relevant concomitant care permitted or prohibited during the trial {11d}

This trial seeks to link YEH to concomitant care, so no care is prohibited.

### Provisions for post-trial care {30}

The trial seeks to link youth to ongoing care that extends beyond trial completion. No provisions are provided once the trial ends.

### Outcomes {12}

Each of the measures below is assessed at baseline, 3, 6, 9, and 12 months in order to determine change over time (Table 1).

**Table 1 Tab1:** Suicide prevention protocol schedule of procedures and assessments

Procedures/assessments	Study period					
	**Allocation**	**Baseline**	**Follow-up**			
			**3 months**	**6 months**	**9 months**	**12 months**
Enrolment:						
Eligibility screen	5 min	X				
Informed consent	5 min	X				
Interventions:						
Service as Usual (SAU)	6 months	X	X	X		
Cognitive Therapy for Suicide Prevention (CTSP) + SAU	6 months	X	X	X		
Assessments						
Locator form	5 min	X	X	X	X	X
Demographic/Homeless Experiences Form (HEF)	10 min	X				
Follow-up Homeless Experiences Form (HEF)	10 min		X	X	X	X
Services contact log	5 min	X	X	X	X	X
The Client Satisfaction Questionnaire (CSQ-8)	10 min	X	X	X	X	X
Scale for Suicide Ideation – Worst (SSI-W)	10 min	X	X	X	X	X
Form 90	20 min	X	X	X	X	X
The Beck Depression Inventory II (BDI-II)	10 min	X	X	X	X	X
Inventory of cognitive distortions	5 min	X	X	X	X	X
The Social Problem-Solving Inventory-revised Short-version (SPSI-R:S)	5 min	X	X	X	X	X
The Coping Inventory for Stressful Situations-Short Form (CISS-SFC)	5 min	X	X	X	X	X
The Distress Tolerance Scale (DTS)	10 min	X	X	X	X	X
The Impulsivity Control Scale (ICS)	5 min	X	X	X	X	X
The Social Network Inventory (SNI)	10 min	X	X	X	X	X
The Interpersonal Needs Questionnaire (INQ)	10 min	X	X	X	X	X
Beck Hopelessness Scale (BHS)	10 min	X	X	X	X	X
Acquired Capability for Suicide Scale (ACSS)	10 min	X	X	X	X	X
WAI (Monthly-5 times)	5 min		X	X		
Cortisol levels	10 min	X	X	X	X	X

#### Primary outcome

Suicide Ideation – Worst total score (SSI-W) [49]

#### Secondary outcomes

Percentage of days alcohol and drug use (Form-90) [50]Depressive symptoms total score from the Beck Depression Inventory II (BDI-II) [51]

#### Primary mediator

Total cognitive distortions score—Inventory of Cognitive Distortions (ICD) [52]

#### Mediating protective factors

Total score from the Social Problem-Solving Inventory-revised Short-version (SPSI-R:S) [53]

#### Mediating risk factors

Total hopelessness scale score (BHS) [54]Total score of suicidal capacity (Acquired Capacity for Suicide Scale (ACSS) [22]Mean frequency of contact across all network members from the Social Network Inventory (SNI) [55]Thwarted belongingness subscale score—the Interpersonal Needs Questionnaire (INQ) [22Total distress tolerance score (DTS) [56]Physiologic stress is measured through cumulative cortisol levels collected and assayed from hair (each 1 cm of hair growth approximates the cumulative cortisol level for the corresponding month)Total coping with stress score from the Coping Inventory for Stressful Situations-Short Form (CISS-SFC) [57]Total impulsivity control score (ICS) [58]

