#### Cognitive Therapy for Suicide Prevention (CTSP) + SAU

In the experimental condition, youth will receive SAU in addition to CTSP [23]. CTSP asserts that maladaptive cognitions lead to maladaptive emotional and behavioral responses. Furthermore, suicidal behaviors rather than underlying conditions are the primary focus. Therefore, CTSP seeks to identify triggers for suicidal behaviors, primarily targeting those cognitions associated with core beliefs and automatic negative thoughts. Therapists help youth replace negative cognitions with alternative, more adaptive ones which are expected to lead to positive behavioral change. CTSP is offered in ten sessions, but, similar to Stanley et al. [37] and Brent et al. [40], youth will be offered up to nine additional maintenance sessions within the first 6 months post-baseline. A crisis plan is developed in the first session and is expanded as therapy progresses. It includes emergency contact numbers as well as positive coping behaviors, such as walking or listening to music that the client can perform alone. Consistent with the Interpersonal Theory of Suicide [41] and Rudd’s theory [19], the experience of prior suicidal behaviors is considered associated with increased risk for future suicide attempts. Therefore, assessment of recent suicidal thoughts and behaviors is conducted every session. Clients in need of additional mental health treatment or services are referred to those respective agencies.

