### Sample size {14}

The power analyses were conducted using the Monte Carlo simulation method [59]. For the LGMs proposed under Aim 1, previous intervention work established a medium to large effect size for treatment differences on suicidal ideation, with *r*s ranging from 0.42 to 0.77 [60] and Cohen’s *d* ranging from 0.64 to 1.03 [61] from 3- to 12-month post-baseline, favoring the cognitive behavioral treatment. Similarly, treatment differences on secondary outcome, depressive symptoms, also have shown medium to large effect sizes, with *d* ranging from 0.39 to 1.24 for depressive symptoms across 6 months [62]. Aim 1 analyses will compare the growth curves of CTSP + SAU to SAU alone. The proposed sample size is 300, assuming an attrition of 10, 15, 15, and 20% at the 3-, 6-, 9-, and 12-month follow-up (Table 2). For the LGMs, under the conditions of continuous outcome variables (e.g., suicidal ideation) and a dichotomous covariate (i.e., two intervention conditions) that has a regression coefficient of 0.20 (medium effect size) for the slope growth factor [59], a sample size of 300 can produce a power of 0.98 to detect the treatment effect on the growth rate of the outcomes. For Aim 2, mediation analyses (path models) are proposed to identify the mechanisms that underlie the treatment effects. Previous clinical trials have reported treatment differences of medium to large (*d* = 0.49 to 0.88) effect sizes for the proposed mediators, such as perceived burdensomeness [61]. Following the three-path mediation model specification suggested by Thoemmes et al. [63], and assuming medium effect sizes for the path coefficients, the proposed sample size can provide sufficient power (0.92) to detect mediation effects.

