#### Secondary mediators: risk and protective factors

The Social Problem-Solving Inventory-revised Short-version (SPSI-R:S) [53] is one of the most widely used self-report instruments for measuring personal perceptions of social problem-solving ability as it relates to suicidal behaviors. This 25-item assesses both constructive/adaptive and dysfunctional problem-solving dimensions. Strong internal consistency and test–retest reliability (Cronbach’s *α* > 0.90 and *r* = 0.91) and concurrent validity with other measures of social problem-solving and depressive symptomatology have been found [64]. The Coping Inventory for Stressful Situations-Short Form (CISS-SFC) assesses stress coping and includes 21-item measuring that yields 3 subscale scores: task-, emotion-, and avoidance-oriented coping [57]. Reliability for the three subscales is 0.90, 0.88, and 0.83, respectively [57]. Using the Physiologic Stress Measure, we measure chronic physiologic stress of youth through cumulative cortisol levels collected and assayed from hair (each 1 cm of hair growth approximates the cumulative cortisol level for the corresponding month). A recent study assessed the validity of the measure and found cortisol levels assayed in 1 cm of hair were correlated (*r* = 0.61, *p* < 0.01) with salivary cortisol measures in which saliva was collected at 3 time points each day for 1 month [65]. To collect the hair samples, approximately 10–75 mg (approximate width of shoelace tip when bunched) of hair [66] is cut with professional shears from the posterior vertex region of the scalp as close to the scalp as possible. The posterior vertex has the lowest variation in cortisol levels and is the preferred area for sampling [66]. Participants will be surveyed on corticosteroid use as these medications may suppress cortisol levels, psychiatric medication use (e.g., antidepressants), and their hair care practices. Hair will be assayed for cortisol level. The Distress Tolerance Scale (DTS) is a 15-item self-report questionnaire examining the degree to which individuals experience negative emotions as intolerable [56]. The DTS demonstrated high internal consistency and concurrent validity [56]. The Impulsivity Control Scale (ICS) was designed to assess the tendency to engage in impulsive behaviors and lack of patience [58]. The internal reliability for the ICS is 0.80, and the total score was found to be significantly associated with suicidality (*r* = 0.43) and aggressiveness (*r* = 0.63) [58]. The Social Network Inventory (SNI) is a modified version of the Network Interview [55]. The SNI has been used in multiple studies with homeless populations and high-risk adolescents. Respondents are asked to answer various questions about people who are important to them, including family members and friends, and with whom they have interacted within the last 6 months. This study will utilize a support contact measure based on the mean frequency of contact across all network members who the respondent indicated as having provided emotional, tangible, or other support. Possible answers range from 0 to 5 with 0 indicating no contact/support in the past 6 months. This instrument has shown test–retest reliabilities of 0.74 to 0.82 for the key SNI variables for homeless populations [67]. The Interpersonal Needs Questionnaire (INQ) is a 25-item self-report scale designed to assess the two components of suicidal desire as conceptualized by the Interpersonal Psychological Theory of Suicide: thwarted belongingness and perceived burdensomeness [22]. The instrument has demonstrated high internal consistency with alpha coefficients ranging from 0.85 to 0.89 [22]. The Beck Hopelessness Scale (BHS) is a self-report instrument that consists of 20 true–false statements designed to assess the extent of positive and negative beliefs about the future during the past week [54]. The BHS is one of the most widely used measures of hopelessness and has demonstrated high internal reliability across diverse clinical and nonclinical populations with Kuder-Richardson reliabilities ranging from 0.87 to 0.93 [54]. The Acquired Capability for Suicide Scale (ACSS) is a 20-item measure [22], based upon the Interpersonal Psychological Theory of Suicide [21], designed to assess fearlessness about lethal self-injury in both clinical and nonclinical samples. The reliability for the ACSS is adequate (*α* = 0.67) [22]. The ACSS total score is strongly correlated with one item from the Beck Scale for Suicide Ideation (BSS) that asks about one’s courage to kill oneself (*r* = 0.79, *p* = 0.007).

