To determine the change mechanisms underlying the treatment effects, a series of mediation models will be estimated. Hypothesis 2a tests whether changes in youths’ cognitive distortions will mediate treatment differences on the outcomes. We expect that CTSP will lead to a decrease in cognitive distortions which will predict reduced suicidal ideation (primary outcome) and reduced substance use and depressive symptoms (secondary outcome). Hypothesis 2b tests the proposed risk and protective factors on the association between cognitive distortion and suicidal ideation as well on secondary outcomes. We expect that lower cognitive distortion at the 3-month follow-up will be associated with higher levels of protective factors and lower levels of risk factors at the 6-month follow-up, which in turn will be related to lower suicidal ideation and secondary outcomes at the 12-month follow-up. In these models, the baseline assessment of the mediators and outcomes will be controlled in the analysis. The product of the coefficient of the path from the independent variable to the primary mediator (a), the coefficient of the path from the primary mediator to the secondary mediator (b_1_), and the coefficient of the path from the secondary mediator to the outcomes (b_2_) will be computed as the indirect (mediation) effect between the treatment and outcomes (ab_1_b_2_). The strength and significance of the mediation will be estimated using a bootstrap sampling method. The mediation model for each outcome variable (primary and secondary) will be tested separately.

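### The coping mediator is fixed as one CISS-SFC total under risk factors, although the protocol describes only three subscales; if those move in different directions the coping pathway is diluted, and the predicted sign is doubtful for coping and wrong for supportive contact

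*Protocol article*

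**What the plan says.** In the protocol article, Outcomes {12}, the list headed "Mediating risk factors" includes "Total coping with stress score from the Coping Inventory for Stressful Situations-Short Form (CISS-SFC"). The section on secondary mediators under Plans for assessment and collection of outcomes {18a} says that the instrument "yields 3 subscale scores: task-, emotion-, and avoidance-oriented coping" and that "Reliability for the three subscales is 0.90, 0.88, and 0.83, respectively". No total score, no reliability for a total and no scoring rule appear there.

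Hypothesis 2b, restated under Study aim 2 in Statistical methods {20a}, expects lower cognitive distortions at 3 months to go with "higher levels of protective factors and lower levels of risk factors at the 6-month follow-up". The indirect effect is the product of three path coefficients, and "The strength and significance of the mediation will be estimated using a bootstrap sampling method". The CTSP description says of the crisis plan: "It includes emergency contact numbers as well as positive coping behaviors, such as walking or listening to music".

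The same risk list holds the Social Network Inventory (SNI) score. The measures section defines this as mean frequency of contact with people who gave support, where zero stands for no contact or support. For the Interpersonal Needs Questionnaire the list names one subscale, thwarted belongingness, so the authors did use subscale scoring where they wanted it.

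**The concern.** Two sections of one document disagree on which coping score will be analysed, and the section that fixes the mediator chooses the version that the other does not describe.

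The choice matters because the names of the three subscales suggest that they need not move together. If lower distortions go with more task-oriented and less emotion-oriented coping, a sum of the two moves less than either part. A null result for coping could then come from the scoring and be reported as a finding about mechanism.

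The risk label raises a separate problem of sign. Read literally, Hypothesis 2b predicts less coping and less supportive contact as the favourable outcome. An increase in supportive contact, which the trial would welcome, would count against its own hypothesis. An undirected coping total could be read either way once the data are known.

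**Working it through.** **1. The plan's own figure.** Sample size {14} states: "assuming medium effect sizes for the path coefficients, the proposed sample size can provide sufficient power (0.92) to detect mediation effects". Numeric path sizes and alpha are not given, so 0.92 cannot be strictly reproduced. I take two-sided alpha 0.05 and approximate the power of one path as Φ(atanh|r|·√(N−3) − 1.96). Chain power is the product of the three path powers; joint significance stands in for the bootstrap.

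- A difference of d = 0.5 corresponds to r = 0.5/√(0.5² + 4) = 0.243.
- All three paths at 0.243 give 0.97 at N = 300, 0.93 at N = 255 (15% attrition) and 0.91 at N = 240 (20% attrition).

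So 0.92 is attainable for a mediator whose score points in one direction. The question is what happens to a composite.

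**2. Inputs for the coping chain (all path values are assumptions).**

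- Treatment to distortions: 0.5 SD, r = 0.243.
- Distortions to a subscale, and subscale to ideation: 0.30 in absolute value.
- N = 300 × (1 − 0.20) = 240.
- Total = equal-weight sum of three standardised subscales with mutual correlation ρ, so SD = √(3 + 6ρ). The cases below use ρ = 0, SD = 1.732.

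**3. One subscale analysed alone.** Path powers are 0.968, 0.997 and 0.997. Chain: 0.968 × 0.997 × 0.997 = 0.96. Simulation (2,000 data sets, all three paths significant) also gives 0.96.

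**4. The total.**

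- Only emotion-oriented coping carries the effect: each total-score path is 0.30/1.732 = 0.173, power 0.77. Chain: 0.968 × 0.77² = 0.57. Simulation gives 0.49 to 0.55.
- Task effect half the size of emotion and opposite: (0.30 − 0.15)/1.732 = 0.087, power 0.27. Chain: 0.968 × 0.27² = 0.07. Simulation gives 0.05.
- Task and emotion equal and opposite, avoidance zero: 0/1.732 = 0. Chain below 0.01. Simulation gives 0.004.

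**5. Range.** With the first path raised to 0.30 and ρ from 0 to 0.4:

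| Case | N = 240 | N = 300 |
|---|---|---|
| One subscale alone | 0.99 | 0.999 |
| Total, emotion only | 0.49–0.59 | 0.60–0.73 |
| Total, equal and opposite, avoidance also moving by 0.30 either way | 0.49–0.59 | 0.60–0.73 |
| Total, half-size opposing | 0.07 | 0.10 |
| Total, exact cancellation | 0.001 | 0.001 |

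Dilution therefore does not need opposing effects: adding two inert subscales already costs a good part of the power. Near-zero power does need exact, or nearly exact, offsetting.

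**6. Direction, set side by side.**

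- Coping total: labelled risk, so predicted to fall. The intervention builds positive coping behaviours, so at least some coping is meant to rise.
- SNI supportive contact: labelled risk, so predicted to fall. Zero is no contact or support, and the background section treats isolation as the risk, so the favourable direction is up.
- Distress Tolerance Scale (DTS): labelled risk. The measures section describes it as the degree to which negative emotions are felt to be intolerable, which is compatible with higher meaning worse. No contradiction is shown.

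**The case against.** The best defence is that the article condenses a fuller protocol, and scoring keys are commonly left there. A total need not be a plain sum, and reverse-scoring is not excluded. The Social Problem-Solving Inventory also spans adaptive and dysfunctional dimensions and is used as a total without complaint. This stands as far as it goes: the power loss above is conditional on a plain sum. It does not remove the mismatch, because the article itself describes three scores and then analyses a fourth.

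It is also fair that the opposing directions are not documented for this instrument. The background text on effective and impeded problem-solving concerns a different construct, and the coping examples for CTSP are crisis-plan items such as walking or music. They do not show that task-oriented coping will rise or emotion-oriented coping fall.

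A reader might infer more than the documents support:

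- *That coping cannot emerge as a mediator.* This holds only under exact or near-exact offsetting; in other cases the effect is weakened.
- *That the risk label prevents detection.* A bootstrapped signed product can be significant in either direction. The label affects the stated prediction and the interpretation, not the test.
- *That distress tolerance is misclassified.* The article's description allows higher to mean worse. Scale names are an unsafe guide: the Impulsivity Control Scale sounds protective, yet the article reports a correlation of 0.43 with suicidality.
- *That power for an arm difference on coping measures the loss.* The planned test is the chain through distortions, so only chain power is relevant.

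**Conclusion.** The concern holds in a limited form. The text is inconsistent on the coping score: a total in the outcome list, three subscales and no total in the measures section. On a plain-sum reading with assumed paths of 0.3 and n = 240, chain power falls from about 0.96 for one subscale to about 0.5, 0.05 or below 0.01, depending on how far the parts offset. These figures rest on assumed path sizes, equal weights and an assumed alpha; they show the risk and do not forecast the result.

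The predicted direction fits poorly for the coping total and is wrong as written for supportive contact. For distress tolerance only the scoring direction needs stating.

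The scope is two of nine secondary mediators in Aim 2. The primary outcome analysis in Aim 1 and the moderator analyses in Aim 3 are untouched. It is worth correcting before analysis because the correction is nearly free and rules out choosing the sign afterwards.

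**What to change.** In Outcomes {12}:

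- Replace the CISS-SFC total with the task-, emotion- and avoidance-oriented subscale scores as separate mediators, each with its predicted direction under Hypothesis 2b. This brings the list into line with the measures section.
- Move SNI supportive contact to the protective list.
- For the DTS, add one phrase saying whether a higher score means more or less tolerance, and keep or move it accordingly.

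If the authors prefer to keep a coping total, they should define how it is formed, including any reverse-scoring, and which direction is favourable.

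The cost is wording plus some extra models. The subscales come from items already collected. Three scores in place of one adds two mediator models per outcome, or 2 × 3 = 6 over ideation, substance use and depressive symptoms. That is a modest increase in the number of mediation tests, to be acknowledged when the results are read.

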#### Moderating variables

Sex at birth, race/ethnicity, sexual orientation (demographic questionnaire), and baseline service connection (services contact log).

### Participant timeline {13}

Participant flow is shown in Table 2. Eight youth will be recruited each month starting in October, 2023, until the entire sample, *N* = 300, is recruited. Study completion occurs 1 year from the last baseline assessment, and youth are assessed at 3, 6, 9, and 12 months post-baseline.

**Table 2 Tab2:** Recruitment and assessments by project year

Year	1	2	3	4	5	Total
Baseline assessments	72	96	96	36	0	300
3-month follow-ups	48	96	96	60	0	300
6-month follow-ups	24	96	96	84	0	300
9-month follow-ups	0	96	96	96	12	300
12-month follow-ups	0	72	96	96	36	300
Total assessment interviews	144	456	480	372	48	1500

### Sample size {14}

The power analyses were conducted using the Monte Carlo simulation method [59]. For the LGMs proposed under Aim 1, previous intervention work established a medium to large effect size for treatment differences on suicidal ideation, with *r*s ranging from 0.42 to 0.77 [60] and Cohen’s *d* ranging from 0.64 to 1.03 [61] from 3- to 12-month post-baseline, favoring the cognitive behavioral treatment. Similarly, treatment differences on secondary outcome, depressive symptoms, also have shown medium to large effect sizes, with *d* ranging from 0.39 to 1.24 for depressive symptoms across 6 months [62]. Aim 1 analyses will compare the growth curves of CTSP + SAU to SAU alone. The proposed sample size is 300, assuming an attrition of 10, 15, 15, and 20% at the 3-, 6-, 9-, and 12-month follow-up (Table 2). For the LGMs, under the conditions of continuous outcome variables (e.g., suicidal ideation) and a dichotomous covariate (i.e., two intervention conditions) that has a regression coefficient of 0.20 (medium effect size) for the slope growth factor [59], a sample size of 300 can produce a power of 0.98 to detect the treatment effect on the growth rate of the outcomes. For Aim 2, mediation analyses (path models) are proposed to identify the mechanisms that underlie the treatment effects. Previous clinical trials have reported treatment differences of medium to large (*d* = 0.49 to 0.88) effect sizes for the proposed mediators, such as perceived burdensomeness [61]. Following the three-path mediation model specification suggested by Thoemmes et al. [63], and assuming medium effect sizes for the path coefficients, the proposed sample size can provide sufficient power (0.92) to detect mediation effects.

